## 6.4 Immunisation schedule

**Table 4 Schedule of doses, formulation and routes of immunisation**

| Study week                            |    | 0                                                                                                                                                   | 4                                                                                                                                                    | 12                                                                                                                                                    | 24                                                                                                                                                                        | 40                                                                                                                                                                         |
|---------------------------------------|----|-----------------------------------------------------------------------------------------------------------------------------------------------------|------------------------------------------------------------------------------------------------------------------------------------------------------|-------------------------------------------------------------------------------------------------------------------------------------------------------|---------------------------------------------------------------------------------------------------------------------------------------------------------------------------|----------------------------------------------------------------------------------------------------------------------------------------------------------------------------|
| Injection schedule in days +/- window |    | 0                                                                                                                                                   | 28 days (+/-3) post DNA I                                                                                                                            | 84 days (+/- 7) post DNA I                                                                                                                            | 84 days (+/-7) post DNA III                                                                                                                                               | 112 days (+/-14) post MVA I                                                                                                                                                |
| Study Group                           | N  | 1 st vaccination                                                                                                                         | 2 nd vaccination                                                                                                                          | 3 rd vaccination                                                                                                                           | 4 th vaccination                                                                                                                                               | 5 th vaccination                                                                                                                                                |
| IA                                    | 60 | DNA I
Zetajet®
2x 0.1ml 3mg/ml [300µg] ID of combined Pools (env/gag) in left (1x 0.1 ml) and right (1x 0.1 ml) arm             | DNA II
Zetajet®
2x 0.1ml 3mg/ml [300µg] ID of combined Pools (env/gag) in left (1x 0.1 ml) and right (1x 0.1 ml) arm             | DNA III
Zetajet®
2x 0.1ml 3mg/ml [300µg] ID of combined Pools (env/gag) in left (1x 0.1 ml) and right (1x 0.1 ml) arm             | MVA I left arm
1x 1ml of 10  pfu MVA IM with (n=30) or without (n=30)
CN54 rgp140GLA-AF right arm
1x 0.4ml [100µg] rgp140/[5µg] GLA-AF | MVA II left arm
1x 1ml of 10  pfu MVA IM with (n=30) or without (n=30)
CN54 rgp140GLA-AF right arm
1x 0.4ml [100µg] rgp140/[5µg] GLA-AF |
| IB                                    | 6  | DNA placebo I
Zetajet®
2x 0.1ml saline ID in left (1x 0.1 ml) and right (1x 0.1 ml) arm                                         | DNA placebo II
Zetajet®
2x 0.1ml saline ID in left (1x 0.1 ml) and right (1x 0.1 ml) arm                                         | DNA placebo III
Zetajet®
2x 0.1ml saline ID in left (1x 0.1 ml) and right (1x 0.1 ml) arm                                         | MVA placebo I left arm
1x 1ml of saline IM with (n=3) or without (n=3)
CN54 rgp140GLA-AF placebo right arm
1x 0.4ml of saline                      | MVA placebo II left arm
1x 1ml of saline IM with (n=3) or without (n=3)
CN54 rgp140GLA-AF placebo right arm
1x 0.4ml of saline                      |
| IIA                                   | 60 | DNA I
Zetajet®+DermaVax™EP
2x 0.1ml 3mg/ml [300µg] ID of combined Pools (env/gag) in left (1x 0.1 ml) and right (1x 0.1 ml) arm | DNA II
Zetajet®+DermaVax™EP
2x 0.1ml 3mg/ml [300µg] ID of combined Pools (env/gag) in left (1x 0.1 ml) and right (1x 0.1 ml) arm | DNA III
Zetajet®+DermaVax™EP
2x 0.1ml 3mg/ml [300µg] ID of combined Pools (env/gag) in left (1x 0.1 ml) and right (1x 0.1 ml) arm | MVA I left arm
1x 1ml of 10  pfu MVA IM with (n=30) or without (n=30)
CN54 rgp140GLA-AF right arm
1x 0.4ml [100µg] rgp140/[5µg] GLA-AF | MVA II left arm
1x 1ml of 10  pfu MVA IM with (n=30) or without (n=30)
CN54 rgp140GLA-AF right arm
1x 0.4ml [100µg] rgp140/[5µg] GLA-AF |
| IIB                                   | 6  | DNA placebo I
Zetajet®+DermaVax™EP
2x 0.1ml saline ID in left (1x 0.1 ml) and right (1x 0.1 ml) arm                             | DNA placebo II
Zetajet®+DermaVax™EP
2x 0.1ml saline ID in left (1x 0.1 ml) and right (1x 0.1 ml) arm                             | DNA placebo III
Zetajet®+DermaVax™EP
2x 0.1ml saline ID in left (1x 0.1 ml) and right (1x 0.1 ml) arm                             | MVA placebo I left arm
1x 1ml of saline IM with (n=3) or without (n=3)
CN54 rgp140GLA-AF placebo right arm
1x 0.4ml of saline                      | MVA placebo II left arm
1x 1ml of saline IM with (n=3) or without (n=3)
CN54 rgp140GLA-AF placebo right arm
1x 0.4ml of saline                      |
| IIIA                                  | 60 | DNA I
Zetajet®+DermaVax™EP
1x 0.1ml 6mg/ml [600µg] ID of combined Pools (env/gag) in left arm                                   | DNA II
Zetajet®+DermaVax™EP
1x 0.1ml 6mg/ml [600µg] ID of combined Pools (env/gag) in left arm                                   | DNA III
Zetajet®+DermaVax™EP
1x 0.1ml 6mg/ml [600µg] ID of combined Pools (env/gag) in left arm                                   | MVA I left arm
1x 1ml of 10  pfu MVA IM with (n=30) or without (n=30)
CN54 rgp140GLA-AF right arm
1x 0.4ml [100µg] rgp140/[5µg] GLA-AF | MVA II left arm
1x 1ml of 10  pfu MVA IM with (n=30) or without (n=30)
CN54 rgp140GLA-AF right arm
1x 0.4ml [100µg] rgp140/[5µg] GLA-AF |
| IIIB                                  | 6  | DNA placebo I
Zetajet®+DermaVax™EP
1x 0.1ml saline ID in left arm                                                               | DNA placebo II
Zetajet®+DermaVax™EP
1x 0.1ml saline ID in left arm                                                               | DNA placebo III
Zetajet®+DermaVax™EP
1x 0.1ml saline ID in left arm                                                               | MVA placebo I left arm
1x 1ml of saline IM with (n=3) or without (n=3)
CN54 rgp140 GLA-AF placebo right arm
1x 0.4ml of saline                     | MVA placebo II left arm
1x 1ml of saline IM with (n=3) or without (n=3)
CN54 rgp140GLA-AF placebo right arm
1x 0.4ml of saline                      |

## 6.5 Dose modifications and discontinuation

There are no planned modifications to dose, other than discontinuation.

The schedule may be modified if a participant has symptoms or signs on the day of scheduled immunisation, and the investigator considers it best to defer the immunisation. The participant will be asked to return for review within the window period of the scheduled immunisations. Examples of the type of symptoms and signs are given in **Table 2** (section 7.5.5 of the protocol).

Any discontinuation and reason for early termination of the immunisation schedule will be discussed with the monitors and the TMG and should be reported to the Sponsor and DSMB within the next 2 working days. Trial participants who are discontinued from additional study injections will continue to be followed according to the schedule to further evaluate safety and monitor adverse events. They will also continue to be covered by the medical/trial insurance until the end of the study period. The frequency of laboratory investigations, e.g. for immunogenicity assessments may be reduced on consultation with the monitors and TMG.

## 6.6 Clinical management of adverse events

The Trial Management Team (TMT) at each study site will assess, manage and treat adverse events as appropriate. Clinical study members include well trained doctors and nurses who are supervised by senior physicians. For adverse events management which exceeds the capacities of the study clinics participants will be referred to appropriate health facilities or independent physicians for further care and treatment at Muhimbili National Hospital (MNH), the Mbeya Referral Hospital (MRH) or Hospital Central de Maputo (HCM). The study clinic will however be responsible for follow up on the medical process of referred participants and will be responsible to report as appropriate as outlined in **section 8**. The Trial Management Group (TMG) will meet at regular intervals during conference calls to discuss any relevant medical or adverse events or reactogenicity and will provide support and advice to the study sites.

## 6.7 Non-trial treatment

Participants will be asked at each visit about medications taken. All medication including other vaccinations (e.g. tetanus toxoid) or herbal/traditional remedies will be recorded in the case record form. Documentation should include the generic name of the drug, indication for use, dose and route of administration, frequency, start and stop dates. For medication available over the counter or other sources, the maximum information available on questioning the volunteer will be recorded. For combination medication it is desirable to include all generic drug names into one entry (e.g. Coartem® = Artemether + Lumefantrine). For herbal or traditional remedies as much information as possible will be sought about the content, the indication or the indigenous name.

The need for the following medications will lead to study discontinuation

- Immunomodulatory agents (i.e. immunoglobulin)
- Immunosuppressive agents (i.e., systemic steroids, chemotherapy)
- Live, attenuated vaccines. Other vaccines (subunit or killed) should be given at least two weeks before or two weeks after HIV immunisation.

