#### Immunological follow-up

Follow-up of HIV infected individuals who have received study vaccine products will be performed according to the study schedule for safety assessment. However, if a participant is found to be HIV-infected during the trial, he/she will be excluded from further immunisations in the trial. The study clinics will work in close collaboration with the HIV clinics providing all relevant clinical and lab information and assisting in CD4 count and viral load monitoring as appropriate. The intensity of assessments will be dependent on clinical progression, including changes in surrogate markers such as CD4 count.

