#### 7.1.2 Visit windows

Immunisation visits are compliant with the protocol if they comply with the following target dates and visit windows:

DNA I (Visit 3, week 0): Day 0

DNA II (Visit 5, week 4): 28 days (+/-3) post DNA I

DNA III (Visit 8, week 12): 84 days (+/- 7) post DNA I

MVA I +/- CN54rgp140/GLA-AF (Visit 11, week 24): 84 days (+/-7) post DNA III

MVA II +/- CN54rgp140/GLA-AF (Visit 14, week 40): 112 days (+/-14) post MVA I +/- CN54rgp140/GLA-AF

If there is a delay >4 weeks, a decision will be made by the TMG as to whether immunisation will continue.

Safety follow up visits performed 14 days (2 weeks) after each immunization (Visits 4, 6, 9, 12 and 15) will be compliant with the protocol if they take place -3 to +3 days of the target date.

Safety follow up visits performed 28 days (4 weeks) after each immunization (Visits 7, 10, 13, 16) will be compliant with the protocol if they take place -5 to +5 days of the target date.

Long term immunogenicity and safety follow up visits are performed 84 days (12 weeks) and optional 168 days (24 weeks) after the last immunization and will be compliant with the protocol if they take place -14 to +14 days of the target date.

The primary endpoint and follow-up visits are scheduled for 2 and 4 weeks after the second MVA immunisation or at week 42 if immunisations have been discontinued will be compliant with the protocol if they take place  $\pm 7$  days either side of the target date respectively.

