## **7.6 Criteria for stopping treatment**

Volunteers/participants may discontinue further immunisations at any time if they wish to do so, for any reason. The date of discontinuation and reason for doing so will be recorded in a case record form.

The clinical investigator may decide that it is not in the best interests of the volunteer/participant to proceed to the next immunization if the investigator deems that

continuing might compromise participant wellbeing or interfere with the achievement of the trial's objectives. Participants who are discontinued due to a clinical or social adverse event (AE) will be followed up until the event has stabilised. The event should be reported as described in **sections 8.2.1 and 8.2.2**.

The following are examples of circumstances in which the clinical investigator would discontinue the injection schedule in a participant:

1. HIV infection
2. Pregnancy
3. Type 1-hypersensitivity associated with immunization.
4. Any medical condition that can recur/deteriorate with further immunizations.
5. Need for systemic glucocorticoids or immunomodulators other than NSAIDs for any reason.
6. The Sponsor, vaccine provider or principal investigator decides to stop or cancel the study.
7. The ethical or regulatory authorities decide that the study be stopped.

Trial volunteers who are discontinued from additional study injections will continue to be followed according to the schedule to further evaluate safety and monitor adverse events, unless they wish to withdraw from the study entirely, in which case they are free to do so. The frequency of visits and laboratory investigations may be reduced on consultation with the Principal Investigator and TMG. Participants who have received any immunisations should be asked to undergo the procedures scheduled for the primary endpoint visit as a minimum. They will also continue to be covered by the medical insurance until the end of the study period.

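### Section 6.7 takes participants who need systemic steroids or immunomodulators out of the study, while section 7.6 stops only their injections and keeps them in follow-up

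*Protocol*

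**What the plan says.** Section 6.7 covers concomitant medication. It introduces three classes of product (immunomodulatory agents, immunosuppressive agents including systemic steroids and chemotherapy, and live attenuated vaccines) with: "The need for the following medications will lead to study discontinuation".

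Section 7.6 lists examples of circumstances in which the investigator would discontinue the injection schedule. Item 5 reads: "Need for systemic glucocorticoids or immunomodulators other than NSAIDs for any reason". On follow-up, the section keeps such participants on schedule, with one exception: "unless they wish to withdraw from the study entirely, in which case they are free to do so". It also permits a lighter schedule ("The frequency of visits and laboratory investigations may be reduced on consultation with the Principal Investigator and TMG") and sets a floor: "Participants who have received any immunisations should be asked to undergo the procedures scheduled for the primary endpoint visit as a minimum".

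Section 6.5 states the same rule for anyone whose injections stop: "Trial participants who are discontinued from additional study injections will continue to be followed according to the schedule". Section 7.1.2 dates the primary endpoint visit relative to the second MVA immunisation, "or at week 42 if immunisations have been discontinued".

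**The concern.** For systemic steroids and immunomodulators, the same clinical event leads either to leaving the study or to stopping injections with follow-up continued, depending on which section a site opens. Section 6.7 is where site staff would look when a participant needs a new medicine, and it has no cross-reference to 6.5 or 7.6.

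Section 9.5.1 defines the intention-to-treat population as everyone randomised who received at least one immunisation. An immunised participant who then needs steroids stays in that population whatever the site does, so ending follow-up creates missing outcome data in the analysis set. It also removes safety observation when that may matter most. Section 6.2 keeps corticosteroids at hand for immediate hypersensitivity reactions, so a need for steroids can arise from a vaccine reaction. Under 9.2.1.2, an adverse event that leads to a decision to stop immunisations is itself part of the primary safety endpoint.

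**Working it through.** No figure in the protocol has to be reproduced. The check compares texts and then counts visits.

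**Step 1: is the trigger the same?** Section 6.7 names immunomodulatory agents and systemic steroids; 7.6 item 5 names systemic glucocorticoids and immunomodulators. These overlap. Chemotherapy and live vaccines appear only in 6.7, so the direct conflict is limited to the overlap.

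**Step 2: is the consequence different?** Section 6.7 refers to the study; 7.6 refers to the injection schedule. Elsewhere the protocol treats these as separate:

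- 7.6 contrasts stopping injections with a participant's own wish to leave altogether. Medication need is not given as an exception to continued follow-up.
- 5.5 lists withdrawal of consent separately from termination of the vaccination schedule.
- 7.5.7 names discontinuing dosing and withdrawing a participant as alternatives.
- HIV infection and pregnancy are also on the 7.6 list, and their own sections stop immunisation but keep safety follow-up. For HIV infection (6.8.2), "he/she will be excluded from further immunisations in the trial" while follow-up for safety continues. Section 7.3.4 treats pregnancy the same way.

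**Step 3: what could be lost per affected participant?** Visits are numbered V1 to V18. V17 (week 52) ends the minimum schedule and V18 (week 64) is optional. After visit k, the visits remaining are 17 − k, or 18 − k with the option. The low end is the 7.6 floor: one visit (V15, week 42) if that visit is still to come, otherwise none. Immunogenicity time points are those in 7.1 after enrolment (weeks 14, 26, 28, 42, 44, and 64 or 52), counting the last once.

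| Trigger arises after | Visits lost, 7.6 floor | Visits lost, full schedule to V17 (V18) | Immunogenicity time points still due |
|---|---|---|---|
| V3 (week 0) | 1 | 17 − 3 = 14 (15) | 6 |
| V11 (week 24) | 1 | 17 − 11 = 6 (7) | 5 |
| V14 (week 40) | 1 | 17 − 14 = 3 (4) | 3 |
| V15 (week 42) | 0 | 17 − 15 = 2 (3) | 2 |

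The range over the minimum schedule is 0 to 14 visits. Appendix 2 also marks antibody sampling at both V17 and V18, and only the large cell draw is either/or. For antibodies, a participant who attends V18 therefore has one time point more than the last column shows.

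After V14 no injections remain. From then on, stopping the injection schedule changes nothing for the participant, while 6.7 taken literally would still end the study for them.

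**The case against.** The strongest reply is that the 6.7 phrase is loose wording that the protocol already resolves. Chapter 6 deals with treatment, and 6.5 uses discontinuation to mean early termination of the immunisation schedule. Section 6.7 does not say that visits cease. When 7.6 means leaving the study, it says so expressly. Appendix 10 records that the withdrawal and discontinuation criteria were condensed into 7.6, which makes that the governing section. For week 42 data to be lost, a site would have to overlook item 5 and the minimum-visit sentence. It would also have to go uncorrected by the monitors and Trial Management Group, with whom 6.5 requires any discontinuation to be discussed; the Sponsor and DSMB must be told within 2 working days. Section 7.6 also follows anyone stopped because of an adverse event until the event has stabilised.

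Much of this stands. The intended rule is clear, and the safeguards make serious loss unlikely. The 7.6 list is headed as examples, and 7.5.7 shows that an investigator may consider withdrawing a participant, so leaving the study is not solely the participant's decision.

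None of it removes the conflict. Section 6.7 is phrased as an operative rule, it names the study and not the injections, and the protocol distinguishes the two elsewhere. A reader has to consult other sections to learn that 6.7 should not be taken at its word.

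**Conclusion.** The contradiction is real and confined to immunomodulatory agents and systemic steroids. Sections 6.5, 7.1.2 and 7.6 agree with one another, and the phrase in 6.7 is the one that is wrong.

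The possible loss is 0 to 14 of the 17 minimum visits per affected participant, including the week 42 and 44 samples if the need arises before V15. This assumes that a site follows 6.7 literally and that the review required by 6.5 does not correct it. The protocol gives no rate of steroid or immunomodulator use, so no effect on power or on any estimate can be calculated. The number affected is probably small in healthy volunteers, and no difference between arms is claimed. The point is minor, with high confidence in the reading of the text.

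**What to change.** In section 6.7, replace the reference to study discontinuation with: discontinuation of further immunisations, with follow-up continued as in sections 6.5 and 7.6. Because the phrase introduces the whole list, the new wording would also cover chemotherapy and live vaccines. That is consistent with 6.5, which continues follow-up for anyone whose injections are stopped. The example list in 7.6 can stay as it is.

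The cost is one phrase. No visits or samples are added, because the follow-up is already in the schedule.

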## 6.8 Issues related to HIV

Samples will be tested at the MUHAS Department of Microbiology/Immunology, the MMRC laboratories and the INS Maputo laboratories using HIV antigen/antibody ELISA. A negative first ELISA will be regarded as a negative HIV test result. Positive results will be confirmed by a duplicated second ELISA. In the case of discordant ELISA results, HIV PCR or Immuno Blot analysis will be performed. Positive or indetermined Immuno Blot results will also be confirmed by HIV PCR. A negative Western Blot or PCR result (HIV RNA negative for qualitative PCR tests or HIV RNA <50 copies/µl for ultrasensitive quantitative PCR test) will be interpreted as HIV uninfected indicating a false positive HIV test response due to HIV vaccination. HIV test results after enrolment will be reported as “infected” or “not infected” to the study clinic in order to maintain blinding procedures for vaccine or placebo recipient.

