### 6.2 Administration of vaccines

The immunizations will take place in an outpatient setting. Prior to each immunization participants will receive a baseline medical status check up including vital signs assessment to confirm the medical eligibility before vaccine administration. Safety lab procedures, urine analysis as well as HIV testing will be performed before vaccine administration. A pregnancy test for female participants will have to show negative results before each immunization.

The study pharmacist will draw the vaccines or placebos into the applicable syringes for the Zetajet devices in case of DNA vaccinations or into syringes for IM use in the case of the MVA and CN54 rgp140/GLA-AF vaccinations according to standardized operational procedures. Prior to use the vials will be thawed at room temperature. Thawed vials will then gently be swirled. Care will be taken not to shake or invert the vials.

Upon receipt of the syringes the study nurse/study doctor will deliver the vaccine.

The DNA vaccines/placebo will be administered in one or two injections ID using the needle free Zetajet® device at weeks 0, 4 and 12. The prepared syringes will be loaded into the Zetajet by the study pharmacist according to manufacturer's instructions. The Zetajet will be applied on the disinfected skin with light pressure. The study agent is expelled under pressure through a micro-orifice at high velocity in a fraction of a second. The study product should be administered as soon as possible after preparation. If this is not possible, the syringe may be stored under refrigeration (2 to 8°C) but the product must be administered within 4 hours after being drawn up into the syringe.

For study groups II and III electroporation using the Derma Vax™ device will be applied immediately after immunization over the injection site according to manufacturer's instructions and SOP. The Derma Vax™ DNA Electroporation System is a device that delivers a tightly controlled and documented series of electrical pulses to the skin between two arrays of 2 mm long needles 4mm apart.

The CMDR-MVA vaccine/placebo boosting will be administered IM using suitable needles and syringes at weeks 24 and 40 into the deltoid muscle of the left arm. The MVA will be given in a dose of  $10^8$  pfu infectious doses in 1 ml volumes (groups IA, IIA, IIIA) or 1 ml sterile saline will be injected (groups IB, IIB, IIIB).

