### 6.8.1 HIV counselling and testing

Only volunteers with a non-reactive antigen/antibody HIV ELISA result will be enrolled. After enrolment HIV testing will be performed before each vaccination and at the long-term follow-up visit at study weeks 52 (Visit 17) and 64 (Visit 18) and whenever a volunteer has the need to establish his/her HIV status. Study participants will receive pre- and post test counselling as well as risk reduction counselling by a trained nurse/counsellor according to country Guidelines. It is possible that participants may develop antibodies and test ‘positive’ in routine commercial HIV ELISA assays following immunisation. The laboratories at MUHAS, Department of Microbiology/Immunology and MMRC and INS Maputo, will conduct molecular tests (HIV-1 PCR) to distinguish between infection and a post-immunisation response required either for clinical management, or at the request of a volunteer.

During the study, participants will be strongly advised to turn to the study clinic if there is any reason to suspect HIV infection for any reason. Should positive routine serological tests be reported from any other clinic participants are strongly urged to get a second opinion from the study clinic. After study completion participants will be advised to attend the study clinic for any further HIV testing to avoid confusion of false positive test results. After the completion of the trial with consecutive unblinding of the Study Groups, participants will receive an individual unblinding session, indicating the Immunisation Group plus false positive HIV test results. In the event of ongoing post-immunisation positive ELISA, the volunteers will be invited to attend a specified centre until such time as this response has disappeared. All participants will be provided with a Trial Participation Card indicating that they have participated in an HIV Vaccine Trial with the potential of false positive HIV tests due to immunization (*see Appendix 7*). This card has no expiration date and must be presented by the volunteer whenever he/she desires to have an HIV test.

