#### Social discrimination as result of a post-vaccine response

The aim is to minimize the possibility of social discrimination in participants who develop a positive HIV ELISA test by providing HIV testing by PCR and certification for volunteers as required. An identification card stating that the individual has participated in a vaccine trial, with a contact number in case of medical emergency, will be provided.

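### Section 6.8 states no next step for two reactive HIV ELISAs after immunisation, and prints its quantitative PCR cut-off per µl

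*Protocol*

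**What the plan says.** Section 6.8 of the protocol gives the HIV testing sequence. A non-reactive first ELISA ends it. For a reactive one, "Positive results will be confirmed by a duplicated second ELISA". The next sentence reads "In the case of discordant ELISA results, HIV PCR or Immuno Blot analysis will be performed", and a positive or indeterminate blot then goes to PCR. A negative blot or PCR is read as uninfected, with the ELISA reactivity put down to vaccination. For a quantitative PCR, negative is defined as "HIV RNA <50 copies/µl for ultrasensitive quantitative PCR test". After enrolment the laboratory sends only a two-way result, infected or not infected, "to the study clinic in order to maintain blinding procedures for vaccine or placebo recipient".

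Other text bears on the same question:

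- Section 6.2: "Safety lab procedures, urine analysis as well as HIV testing will be performed before vaccine administration".
- Section 6.8.1 accepts that participants may become ELISA-positive through immunisation. It says the three laboratories will run "molecular tests (HIV-1 PCR) to distinguish between infection and a post-immunisation response required either for clinical management", or when a volunteer asks.
- Section 6.8.2, on social discrimination, aims to protect "participants who develop a positive HIV ELISA test by providing HIV testing by PCR and certification for volunteers as required".
- Section 6.8.2, on immunological follow-up: "if a participant is found to be HIV-infected during the trial, he/she will be excluded from further immunisations in the trial".
- Appendix 2 has a block for the HIV test algorithm whose single row names ELISA, Western blot and PCR together. It is marked at every HIV-test visit and drawn from the haematology tube.

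**The concern.** In an HIV vaccine trial, two reactive ELISAs are a foreseeable vaccine effect. Appendix 9 reports that the sera of all vaccinees in the earlier Tanzanian trial of the same DNA and MVA reacted in diagnostic serology. That is the pattern for which section 6.8 names no further test.

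The clinic sees only the two-way result, so it cannot tell whether a report of infection rests on ELISA alone or on PCR. If such a report reached the clinic before an immunisation, the participant could lose that dose and be referred for HIV care. A missed dose also removes the participant from the per-protocol population defined in section 9.5.1.

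The printed PCR cut-off errs in the other direction. Taken literally, it would let a participant with substantial viraemia be read as uninfected.

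**Working it through.** **1. The branches of section 6.8**

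| First ELISA | Repeat ELISA | Next step stated in 6.8 |
|---|---|---|
| Negative | not done | Read as negative |
| Reactive | Discordant | PCR or immunoblot; a positive or indeterminate blot goes to PCR |
| Reactive | Reactive | None |

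In the third row the only wording is that the second ELISA confirms the first. After a reactive ELISA, the only stated ground for uninfected is a negative blot or PCR, and this row is not sent to either. Equally, no sentence says that this row means infected.

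**2. Whether other text fills the third row**

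- Section 6.8.1 commits the laboratories to PCR, but ties it to clinical management or a volunteer's request.
- Section 6.8.2 offers PCR, but only as required.
- Appendix 2 lists PCR at each HIV-test visit, without saying which results go on to it.
- Consent item 8 (section 4.4) and section 12.1 say that the distinction can be made, not when.

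All point to PCR as the deciding test. None places it before the report to the clinic.

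**3. Which tests can cost a dose**

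From section 6.8.1 and Appendix 2, the HIV tests after the first immunisation are:

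- before an immunisation: V5, V8, V11, V14 = 4
- after the last immunisation: V17 and V18 = 2

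Only the first four can cost an immunisation. V5, V8 and V11 follow DNA alone; only V14 (week 40) follows an MVA dose.

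**4. Whether a number affected can be derived**

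It cannot. The Appendix 9 statement on diagnostic serology gives no time point and no repeat-ELISA result. The same appendix reports that in the Swedish trials, after three DNA doses and one MVA dose (the stage corresponding to V14), 57% had Gag-specific and 5% Env-specific antibodies. It does not say that these were results of the diagnostic ELISA used here. About half of the active recipients in this trial also receive an Env protein with the first MVA dose. These figures make reactivity at V14 plausible but do not convert into a rate of two reactive ELISAs.

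**5. The PCR unit**

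- As printed: 50 copies/µl × 1,000 µl/mL = 50,000 copies/mL.
- If per mL was meant: 50 copies/mL.
- Ratio: 50,000 / 50 = 1,000.

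The protocol gives no other value for this cut-off, so the per-mL reading is an assumption. It rests on the assay being called ultrasensitive, which does not fit a limit of 50,000 copies/mL.

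**The case against.** The strongest reply is that section 6.8 is silent here rather than wrong. A reader might infer that it treats two reactive ELISAs as proven infection. The documents do not support that. The sentence on the second ELISA can mean that it confirms ELISA reactivity. A procedure that will not accept a positive immunoblot without PCR is hard to read as accepting two ELISAs. The section itself foresees false positives from vaccination, and reporting vaccine responders as infected would defeat its stated blinding purpose. Section 6.8.1 follows directly, and stopping immunisation and referring someone for HIV care can fairly be called clinical management. All of this stands.

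The reply also notes that safeguards follow a wrong report: expedited reporting within 24 hours (section 8.2), discussion with monitors and the TMG (section 6.5), specialist referral with further investigations (section 6.8.2), and a ±14-day window for the second boost with TMG review of longer delays (section 7.1.2). This makes later correction likely. It does not close the gap, because none of these steps requires a PCR before the report.

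A reader might also infer that most or all of the 180 active recipients risk losing a boost. That would need a rate of dual reactivity before week 40, which the protocol does not give.

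On the unit, the reply is that it is an obvious slip on which nobody would act. A text-reading error in the symbol also cannot be excluded. That lowers the risk, but the figure is a decision threshold for participant safety and is worth checking.

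**Conclusion.** The point holds as a gap and an inconsistency. Section 6.8 names no next step for concordantly reactive ELISAs after immunisation, while sections 6.8.1 and 6.8.2 and Appendix 2 show that PCR is intended to decide. No text puts PCR before the result is reported. The quantitative cut-off is printed 1,000 times higher than the value very probably meant.

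Harm depends on a laboratory applying section 6.8 in isolation, without section 6.8.1 or Appendix 2, and for a lost dose also on the later safeguards not correcting the report in time. A laboratory SOP, which is not at hand, may already close the gap. How many participants would be affected cannot be stated. Sample size, power and the primary analysis are untouched. This is a minor safety correction.

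**What to change.** Amend section 6.8, and the laboratory SOP if it follows the same wording, in three places:

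1. Extend the trigger for further testing to results that are discordant, or concordantly reactive after the first immunisation.
2. After enrolment, require a positive PCR before infection is reported to the clinic.
3. Check the unit of the quantitative PCR cut-off and print it per mL if that was meant.

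The ELISA route at screening can stay, since only non-reactive volunteers are enrolled.

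The cost is small. The laboratories already perform the PCR, and Appendix 2 already draws the blood. There will be some extra PCR runs and a short wait before immunisation. The window is ±14 days at V14 and ±7 days at V8 and V11, but only ±3 days at V5, where a single DNA dose has been given. A report held back for PCR could hint to blinded clinic staff that a participant is seroreactive, and so probably vaccinated. Release of results should therefore be timed so that a delay carries no information, for example with one common turnaround for all HIV results at a visit. The price is that participants with non-reactive results may wait too.
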